**Results:**

The research received funds in August 2022, and participant recruitment began in September 2022. The sample size will consist of 95 mother-child pairs. As of September 2023, 68 participants have been recruited.

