In this scenario, the first meeting takes place on the pediatric evaluation date, which is a scheduled appointment at the Human Milk Bank (BLH) of IFF, at the time of maternity discharge, by the pediatric team. Between one and two days before the scheduled date, the project team contacts the postpartum mother to confirm her attendance at the appointment or reschedule it, aiming to prevent any losses due to forgetfulness or an inability to attend the originally scheduled date.

For postpartum mothers outside the IFF, promotion is being conducted among the team’s contacts through messaging apps and social media. Our outreach encourages interested pregnant individuals to register via an online form to assess eligibility and the expected delivery date. Closer to the expected delivery date, we contact the pregnant individuals to confirm their interest and schedule their participation. A new eligibility check is done by phone one day before the scheduled date to prevent unnecessary travel. If a woman has already given birth when she receives the promotion, we encourage her to contact a team member directly by phone, where eligibility criteria are assessed, and the evaluation is scheduled.

At the end of each assessment, postpartum mothers are scheduled for the next follow-up. To minimize follow-up losses, all participants are contacted via messaging apps or phone for confirmation or rescheduling. Another strategy to increase adherence includes sending a monthly image congratulating them on another month of their baby’s life on the baby’s birth date. This image also contains general information about the baby’s health during that period, such as developmental milestones, feeding, and vaccinations.

The participants started to be recruited in September 2022. Recruitment was open until the desired sample size is achieved (n = 117), which happened in July 2024. The follow-up will continue until all participants reach the one-year postpartum mark, projected to occur in July 2025.

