### Sample size

To assess differences in adipocytokines in human milk according to infant development, the reference was the global score of cognitive development in the communication domain. A previous study assumed that the standard deviation of the score is 13.6 for children of 6 months [53]. We will consider a difference of 3 points significant, and we aim for a significance level of 5% to detect differences if they exist.

Applying the formula for determining the sample size based on an estimate of the population mean, n=[(Zα/2.σ)/e]^2, where Z_α/2_ = 1.96, e = 3 and σ = 13.6 (standard deviation), we obtain N = 79 [54]. If we estimate a follow-up loss of approximately 35%, the sample size (N) should be 117 mother-child pairs.

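### The abstract gives a sample size of 95 pairs and the Methods 117, and 117 falls slightly short of the 122 implied by 79 pairs and a 35% loss

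*Protocol article*

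**What the plan says.** The protocol article gives the planned number of mother-child pairs in three places.

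- Abstract, Results: "The sample size will consist of 95 mother-child pairs". The same paragraph reports 68 recruited as of September 2023.
- Methods, end of the recruitment text (before the variables are described): "Recruitment was open until the desired sample size is achieved (n = 117), which happened in July 2024".
- Methods, Sample size: "If we estimate a follow-up loss of approximately 35%, the sample size (N) should be 117 mother-child pairs".

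The Sample size section also shows how the number before inflation was obtained. It is described as "Applying the formula for determining the sample size based on an estimate of the population mean", with inputs and result "1.96, e = 3 and σ = 13.6 (standard deviation), we obtain N = 79". The Discussion then relies on this calculation when it says that the sample is large enough for the primary objectives, and it names loss to follow-up and the small sample as the main limitations.

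**The concern.** Two things do not fit.

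First, one document states two different totals for the same planned quantity. The 95 is worded as the total to come, not as a dated count, so it cannot be read as progress towards 117. Someone comparing achieved with planned enrolment would find the study exactly on target by the Methods and 22 pairs over target by the abstract (22/95 = 23%).

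Second, the step from 79 to 117 does not match the loss stated beside it. The Discussion names loss to follow-up as a main limitation, so the loss that the enrolled number can absorb should be stated correctly.

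**Working it through.** **Inputs** (all from the Sample size section unless noted): Z = 1.96 for a two-sided 5% level; margin e = 3 points; standard deviation 13.6, taken from a previous study of children at 6 months; loss of approximately 35%; inflated total 117. The abstract supplies 95.

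**Step 1: reproduce the base number.** n = (Z × SD / e)² = (1.96 × 13.6 / 3)² = 78.95, rounded up to 79. The plan's 79 is reproduced.

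**Step 2: inflate for 35% loss.**
- To keep n after a proportion d is lost, enrol n/(1 − d): 79/0.65 = 121.5, so 122. The unrounded 78.95 gives 121.46, also 122.
- The cruder form n × (1 + d) gives 79 × 1.35 = 106.7, so 107.
- Neither gives 117. It is 5 below the first and 10 above the second.

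**Step 3: find the loss that 117 covers.** 1 − 79/117 = 0.325. So 117 pairs keep 79 up to a loss of about 32.5%.

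**Step 4: find what 117 leaves at the stated 35%.** 117 × 0.65 = 76.05, about 76 pairs, which is 3 fewer than 79. On the plan's own precision formula the half-width is 1.96 × 13.6 / √76 = 3.06 points, against the intended 3.00. That is about 2% wider.

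**Step 5: compare the stated totals.**

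| Place | Total | Status |
|---|---|---|
| Abstract, Results | 95 | future total, no derivation given |
| Methods, recruitment text | 117 | target, reached July 2024 |
| Methods, Sample size | 117 | derived from 79 and a loss of approximately 35% |

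The difference is 117 − 95 = 22 pairs. No rounding of the 35% accounts for it, and the article offers no explanation. Numerically, 79 × 1.2 = 94.8, which rounds up to 95. An allowance of 20% applied by multiplication is therefore one possible origin, but no such allowance appears in the article.

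**The case against.** **The inflation gap is minor.** The section says approximately 35%, and 32.5% is only 2.5 percentage points away from a rough planning guess. The cost is 3 pairs and 0.06 points of half-width. This objection stands, and it is why the inflation step comes second. The stated figures still do not follow from one another, and the correction is a single sentence.

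**The real target is not in doubt.** This also stands. Two places in the Methods agree on 117 and recruitment closed there. The only recruitment date in the abstract's Results paragraph is September 2023, so that paragraph looks like an older status report. A reader might infer that the target cannot be determined, but the Methods do not support that. What remains is an uncorrected figure in the part of the article that is read most.

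**Three further inferences are tempting and unsupported.**
- That 95 would fall far short of 79 at a 35% loss. The article attaches 35% only to 117, and 95 was not the number at which recruitment closed.
- That the target was raised from 95 because an earlier 20% allowance was abandoned. The arithmetic fits, but nothing states it. The full protocols, listed as supporting information under Ethical issues, are not shown here and may hold the history.
- That the analysis will have fewer than 79 pairs. The Sample size section does not say at which visit the 35% applies. The Bayley scales are given at 6 and 12 months, and the planned mixed-effects model can use a pair seen only at 6 months. The figure of 76 checks the plan's arithmetic and does not forecast the analysed sample.

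**Conclusion.** The concern holds in two parts of unequal weight. The main one is the contradiction between 95 in the abstract and 117 in the Methods: 22 pairs, unexplained, in a key design figure. The lesser one is that 117 does not follow from 79 and 35%. The standard calculation gives 122, and 117 covers about 32.5%. At 35%, about 76 pairs remain and the half-width is about 3.06 instead of 3.00 points, which changes nothing of substance.

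Both parts should be corrected because the figures are wrong as written and the Discussion leans on them. Neither invalidates the study or calls for more participants.

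The conclusion takes the plan's formula, its standard deviation of 13.6 and its margin of 3 points as given. The formula sets the precision of one mean and has no power term. That is a separate matter and does not affect this point.

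**What to change.** Recruitment is closed, so the correction restates figures and asks for no further enrolment.

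1. In the abstract, replace 95 by 117. If the target was changed during the study, say so and give the date and the reason. If 95 was simply an error, correcting it is enough.
2. In the Sample size section, use one of two wordings: either that 117 pairs allow for a loss of about 32.5% while keeping 79, or that at a 35% loss about 76 pairs are expected, with a precision of about ±3.06 points.

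The cost is a few sentences. The stated tolerance for loss becomes slightly less favourable, and design, conduct and analysis stay as they are.

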### Data entry and statistical analysis

The collected data is being entered into the database using data entry masks specifically developed for the study in the RedCap software. Data storage and backup are provided by application and database servers located in the secure room of COGETIC/Fiocruz, with security levels in compliance with current legislation. A full backup is performed daily, and log backups are done hourly every day from 08:00 to 18:00.

The statistical analyses will be conducted using the Stata statistical software package [55]. Initially, data will be evaluated through a dispersion analysis. The normality of the data will be assessed using the Shapiro-Wilk test, and non-normally distributed variables will be subjected to a logarithmic transformation for subsequent analysis using parametric tests. Proportions of categorical variables will be compared using the chi-squared test, and differences between means of continuous variables will be tested with the Student’s t-test or ANOVA. Pearson’s correlation coefficient will be used to analyze the correlation between continuous variables, such as the correlation between adiponectin and leptin in plasma and milk.

The main variables (adiponectin and leptin concentrations, development scores, and depressive symptoms) will be treated as continuous. To assess the association between these variables, a longitudinal mixed-effects model (LME) will be used, adjusted for confounding factors. LME is a model capable of capturing changes within and between individuals, accommodating time-dependent and independent covariates, accounting for the correlation between repeated measurements in the same individual, and allowing for unbalanced time intervals. The total variance will be estimated by two components: the first measures the variance between individuals at the same time, and the second component measures the within-individual variance between each time point during follow-up. Postpartum time will be included as a fixed and random effect variable. If the response is described by a nonlinear function, a quadratic term will be included in the model.

To determine the model’s adjustment variables, a Directed Acyclic Graph (DAG) will be constructed using the online software DAGitty [56]. The purpose of the DAG is to improve our understanding of the association between exposure and outcome, along with all potential confounding factors. This approach allows us to identify the minimally sufficient adjustment required to estimate the direct effect of plasma adiponectin concentrations on infant neurodevelopment.

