#### Maternal mental health (outcome 2)

Maternal mental health is monitored in all waves of follow-up: up to 15 days, 2, 6, and 12 months postpartum. During the first appointment, data are collected regarding the postpartum mother’s history of depression, as well as her family history of depression. A validated version of the Edinburgh Postnatal Depression Scale (EPDS) is employed. The EPDS was developed by Cox et al. [35] and translated and validated into Portuguese by Santos et al. [36] and consists of a self-report instrument composed of 10 statements, with scored options from 0 to 3 based on the presence and intensity of depressive symptoms.

Many studies cite and use the EPDS because it is a questionnaire that is easy to administer and understand for women, and it has proven to be highly effective in identifying postpartum depression [37–40]. At baseline, the EPDS will be administered by trained interviewers (health professionals or undergraduate students in the healthcare field). In the subsequent follow-ups, participants will receive the EPDS online, via email and/or messaging app, seven days before the in-person meeting, allowing them to self-complete the questionnaire. If a participant does not respond to the online questionnaire, the scale will be administered by trained interviewers on the day of the in-person meeting.

Additionally, depression is assessed using the Beck Depression Inventory-II (BDI-II) at 6 and 12 months postpartum. This is because the validation of the Brazilian version of the EPDS was only conducted with women up to 3 months postpartum. The BDI-II is a widely used instrument worldwide and has been validated for the Brazilian population [41]. The application will be conducted by a trained psychologist.

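### The blanket log rule for variables failing Shapiro-Wilk cannot be applied to EPDS totals of 0, and it tests the wrong thing for the mixed model

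*Protocol article*

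**What the plan says.** In the Protocol article, Data entry and statistical analysis, the software is named first: "The statistical analyses will be conducted using the Stata statistical software package". A Shapiro-Wilk screen for normality follows, and the consequence of failing it is fixed in the same sentence: "non-normally distributed variables will be subjected to a logarithmic transformation for subsequent analysis using parametric tests". The tests then listed are the chi-squared test, Student's t-test, ANOVA and Pearson's correlation.

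The next paragraph of the same section says: "The main variables (adiponectin and leptin concentrations, development scores, and depressive symptoms) will be treated as continuous". For associations among these variables, "a longitudinal mixed-effects model (LME) will be used, adjusted for confounding factors". That paragraph does not mention transformation.

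Under Maternal mental health (outcome 2), the EPDS is described as "composed of 10 statements, with scored options from 0 to 3 based on the presence and intensity of depressive symptoms" and is collected at all four visits. In addition, "depression is assessed using the Beck Depression Inventory-II (BDI-II) at 6 and 12 months postpartum". The range of the BDI-II is not given.

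**The concern.** Three features of the text do not fit together.

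- **The rule meets a score that can be 0.** Depressive symptoms are a main variable handled as continuous, and no variable is exempt from the log rule. A plain log of an EPDS total of 0 does not exist, and Stata returns a missing value.
- **The records lost would not be random.** They would be the lowest values of the outcome, so selection would be on the outcome.
- **The criterion is the wrong one for the main model.** A linear mixed model assumes roughly normal residuals and random effects. A right-skewed raw outcome does not by itself breach that assumption, and a normal raw outcome does not guarantee it. The rule also lets a p-value from the study data decide the scale of each main variable.

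At stake is whether the depression results describe the full range of symptoms, and whether they are reported on the EPDS scale or on a log scale chosen after the data were seen.

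**Working it through.** **Sample size for the Shapiro-Wilk check.** The plan's own formula (Sample size) gives n = (1.96 × 13.6 / 3)² = 78.95, rounded up to 79, which reproduces the stated figure. It serves here only as the number of scores tested. The recruitment target is 117.

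**Minimum of the EPDS.** Ten items scored 0 to 3 give 10 × 0 = 0 up to 10 × 3 = 30. A total of 0 is attainable, and log(0) is undefined.

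**Inputs that must be assumed.** The document gives no EPDS mean, SD or shape, and no significance level for the Shapiro-Wilk test (0.05 assumed). Low scores are plausible because Methods makes women on psychiatric medication ineligible, but that does not fix a mean.

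**Share of zeros, negative binomial assumption.** With mean m and SD s, the size is r = m²/(s² − m), the probability parameter is p = m/s², and P(0) = p^r. For m = 5 and s = 4.5: r = 25/15.25 = 1.639, p = 5/20.25 = 0.247, P(0) = 0.101.

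**Trigger and result of the log.** Simulated samples of 79, scores capped at 30:

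| Assumed mean, SD | P(0) | Raw score rejected | Plain log, zeros dropped: rejected | log(x+1): rejected |
|---|---|---|---|---|
| 5, 4.5 | 10.1% | 100% | 94% | 90% |
| 6, 4.5 | 4.6% | over 99% | 88% | 75% |
| 7, 5 | 3.1% | 99% | 82% | 72% |
| 8, 5 | 1.4% | 96% | 82% | 71% |
| 10, 5 | 0.2% | 78% | 78% | 63% |
| 12, 5 | under 0.1% | 58% | 67% | 53% |

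**Sensitivity to the assumed shape.** A beta-binomial on 0 to 30 gives the following:

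- At means of 4 to 7, rejection is 99% to 100% at n = 79, with 5.0% to 13.3% zeros.
- At mean 9, SD 5, rejection is 68% at n = 79 and 90% at n = 117, with 1.2% zeros.
- At mean 12, SD 5, rejection is 19% at n = 79 and 31% at n = 117, with 0.1% zeros.
- After either form of log, Shapiro-Wilk still rejects in more than 90% of samples in all these EPDS settings.

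**In visits.** At means of 5 to 8 (negative binomial) and full attendance:

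- All four visits: 117 × 4 = 468 scores. 468 × 0.014 = about 6 zeros, and 468 × 0.101 = about 47.
- Visits with blood only (T0, T2 and T3, the visits that matter for plasma adipokines): 117 × 3 = 351 scores. 351 × 0.014 = about 5 zeros, and 351 × 0.101 = about 35.

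Attrition would lower both counts. The plan allows for about 35% loss.

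**The case against.** The strongest reply is that the text does not clearly send logged EPDS scores into the main model. The rule is worded for parametric tests, and the listed tests are simple ones. The mixed model has its own paragraph, which only says that the main variables are continuous. Deletion is not stated either. It requires a plain log, and log(x+1) is neither stated nor excluded. The full protocols are supporting files not seen here, and an offset could be specified there or in an analysis plan.

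Much of this stands, and it rules out several stronger readings that a reader might infer.

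- **That symptom-free women are removed from the depression analysis.** In the mixed model, what could be lost is a visit with a score of 0. A woman leaves entirely only if every usable visit scores 0. She would drop out of a single-visit t-test, ANOVA or correlation.
- **That the trigger is certain.** It depends on the distribution. At a mean near 12 it occurs in 19% to 58% of simulated samples of 79, depending on the shape assumed, and zeros are then negligible.
- **That the BDI-II fails in the same way.** Its minimum is not in the document, so only the EPDS part can be verified.
- **That a known amount of power is lost, or a known attenuation arises, in the mixed model.** Simulations of a single visit do not establish this. In them, dropping zeros on the raw scale cost only 1 to 7 percentage points of power, and log(x+1) lowered power with no record dropped. Part of any loss therefore comes from the log scale itself. No mixed model was simulated.

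The reply does not remove the defect. The article states a rule without exceptions, and the rule cannot be carried out on an EPDS total of 0. Any later document would have to amend or patch it. An offset prevents the deletion but usually leaves the score non-normal by the plan's own test. If the rule is meant to stop short of the mixed model, the text should say so.

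**Conclusion.** The point holds in limited form. As written, the log rule cannot be applied to EPDS totals of 0, and it would probably be triggered if scores are low and skewed. Without an offset, zero-score visits would be lost from any analysis of the logged score, selectively at the low end. With an offset, the log would still usually miss its aim. Screening raw variables is the wrong criterion if the rule extends to the mixed model, and the text leaves that open.

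The size is conditional. Under assumed EPDS means of 5 to 8 (SD 4.5 to 5), about 1% to 10% of scores are 0; at means of 10 or more, almost none are. The impossibility of log(0) and the mismatch of criterion rest on the document and on the model's assumptions. The percentages rest on an assumed distribution, independent scores within each sample, and a test level of 0.05. This should be fixed, but it does not threaten the study.

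**What to change.** - Remove the Shapiro-Wilk trigger for the main variables.
- State in advance that adiponectin and leptin concentrations are log-transformed.
- Analyse EPDS, BDI-II and BSID-III on their own scales in the mixed model. This also keeps BSID-III in the points used for the 3-point difference in the sample size section.
- Judge fit from the model residuals, and use robust or bootstrap standard errors if they are skewed.
- Optionally, add a count or ordinal mixed model for the depression scores as a sensitivity analysis.
- If any transformation rule is kept for the simple tests, say that it is confined to them and how zeros are handled.

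The cost is a change of text and slightly more analysis work. No data collection changes. The revision should be made before the outcome data are analysed.

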**Objectives:**

To assess the correlation between adiponectin and leptin in maternal plasma and breast milk and their association with: infant neurodevelopment at 6 and 12 months of age; and maternal mental health over the first year postpartum.

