The role of adipokines in the central nervous system has been the focus of numerous studies over the last decade. In vitro studies demonstrate the role of adiponectin and leptin in stimulating neurogenesis, regulating the proliferation of hippocampal cells in a time- and dose-dependent manner [33,34]. Hence, the promotion of neurogenesis is a potential mechanism through which these adipokines can act on both stimulating infant neurodevelopment and inhibiting postpartum depressive symptoms. Additionally, adiponectin may indirectly influence depression through its actions on the hypothalamic-pituitary-adrenocortical axis (suppression of TNFα) and/or thyroid-mediated effects [13].

Given the scarcity of studies on this subject, the current project stands out for its potential innovation and ability to generate evidence that can assist in understanding and preventing developmental issues in childhood and throughout the life cycle. It also aims to contribute to the search for new strategies to prevent and treat postpartum depression.

In this way, the project seeks to clarify the relationship between adiponectin and leptin in maternal plasma and breast milk, maternal mental health, and infant neurodevelopment. This is based on the hypothesis that plasma concentrations of adiponectin and leptin are associated with the mental health of the breastfeeding mother and are correlated with the concentrations of these adipokines in breast milk. In turn, the consumption of milk with higher concentrations of adiponectin and lower leptin is expected to lead to greater neural stimulation in the infant, promoting better neurodevelopment.

In summary, the research questions to be responded to are: What is the relationship between maternal mental health and the concentrations of adiponectin and leptin in maternal plasma? How are the concentrations of adiponectin and leptin in maternal plasma related to their levels in breast milk? Does the consumption of breast milk with higher adiponectin and lower leptin concentrations result in improved neurodevelopmental outcomes in infants? What role do adiponectin and leptin play in the neurodevelopment of infants, particularly in the context of maternal mental health? These questions aim to dissect the intricate connections between maternal health, breast milk composition, and infant neurodevelopment, offering potential pathways for improving child health outcomes through targeted maternal support.

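### The adjustment set is chosen for the direct effect of plasma adiponectin, which would take the hypothesised milk pathway out of the plasma–neurodevelopment estimate

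*Protocol article*

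**What the plan says.** Under Data entry and statistical analysis, the article gives one way of choosing covariates for the adjusted mixed models: "To determine the model’s adjustment variables, a Directed Acyclic Graph (DAG) will be constructed". The general purpose is to "improve our understanding of the association between exposure and outcome, along with all potential confounding factors". The section then names the target, which is the "minimally sufficient adjustment required to estimate the direct effect of plasma adiponectin concentrations on infant neurodevelopment". No other target effect is named.

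The Introduction sets out the hypothesis in two steps. Plasma adiponectin and leptin are held to be associated with maternal mental health and, the text adds, "are correlated with the concentrations of these adipokines in breast milk". The second step concerns the infant: "the consumption of milk with higher concentrations of adiponectin and lower leptin is expected to lead to greater neural stimulation in the infant".

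The abstract's objectives are wider than the named target. They start "To assess the correlation between adiponectin and leptin in maternal plasma and breast milk and their association with" and list two outcomes: "infant neurodevelopment at 6 and 12 months of age; and maternal mental health over the first year postpartum". The Methods label both blood and milk samples as the main exposure, and the sample-size section is framed on adipocytokines in human milk.

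**The concern.** In a causal diagram, direct effect and total effect are distinct targets with different adjustment sets. A set for the total effect closes confounding paths and leaves mediators alone. A set for the direct effect also closes the paths that run through mediators. The Introduction's hypothesis reads as a chain from plasma adipokine to milk adipokine to infant, so milk adiponectin lies on the path from plasma adiponectin to neurodevelopment. An analyst who enters that chain in DAGitty and asks for the direct effect will be told to condition on milk adiponectin.

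The resulting plasma coefficient would answer a different question: what plasma adiponectin does by routes other than those adjusted for. Read as the effect of plasma adiponectin on infant development, it would understate the effect whenever the milk route carries some of it in the same direction as the rest. The Discussion foresees plasma adipokines as possible biomarkers for infant neurodevelopment, so a misread plasma coefficient would matter.

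**Working it through.** The plan gives no figure on this point, so there is none to reproduce. The check is a comparison of passages, a path identity and a numerical illustration.

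**Passages side by side**

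- Plasma to milk: hypothesised in the Introduction.
- Milk to infant: hypothesised in the Introduction.
- Target of the adjustment set: direct effect of plasma adiponectin on the infant (Data entry and statistical analysis).

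The first two make milk a mediator. The third asks for the effect with mediated paths closed.

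**Path identity.** Let *a* be the effect of plasma on milk, *b* the effect of milk on neurodevelopment, and *c* the effect of plasma by any route not through milk. In a linear model:

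- total effect of plasma = *c* + *a* × *b*
- plasma effect after conditioning on milk = *c*
- amount removed = *a* × *b*

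The amount removed does not depend on *c*. The remainder is zero only if *c* = 0.

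**Illustration in Bayley points.** All inputs are assumed: *b* = 3 points per SD of milk adiponectin, *a* = 0.5 or 0.7, *c* = 0. The 3 points is not an effect per SD taken from the protocol. The article uses 3 only as the difference in its sample-size formula. The outcome SD in the simulation is 13.6, from the sample-size section.

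| Plasma–milk correlation | Total effect, *a* × *b* | Simulated, milk not in model | Simulated, milk in model |
|---|---|---|---|
| 0.5 | 0.5 × 3 = 1.5 | 1.50 | 0.03 |
| 0.7 | 0.7 × 3 = 2.1 | 2.06 | −0.06 |

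The simulation used 200,000 observations. The small departures from zero in the last column are simulation noise.

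**Same check on a standardised scale.** Assumed *b* = 0.30 and *c* = 0, with 1,000,000 observations:

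| *a* | *a* × *b* | Plasma slope, milk not in model | Plasma slope, milk in model | Milk slope, same model |
|---|---|---|---|---|
| 0.3 | 0.09 | 0.090 | 0.000 | 0.301 |
| 0.5 | 0.15 | 0.150 | 0.001 | 0.298 |
| 0.7 | 0.21 | 0.211 | 0.002 | 0.299 |

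The last column limits the point. The model that returns nothing for plasma still recovers the milk effect in full.

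**If plasma also acts by another route.** Suppose *c* equals *a* × *b*. With *a* = 0.5 and *b* = 3, the total is 1.5 + 1.5 = 3.0 points per SD and the direct-effect model returns 1.5. Half of the effect is removed, not all of it.

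**The case against.** The strongest reply is that mediator adjustment is inferred from one word. No section lists milk as a covariate. The mixed models are described as adjusted for confounding factors, and the sentence just before the named target speaks of confounders. The diagram is still to be drawn, and the authors may have used direct effect loosely for a confounder-adjusted effect. That reading is plausible, and it is why the point concerns what happens if the rule is followed as written. It does not remove the mismatch: in a paragraph about DAGitty and minimally sufficient sets the term has a defined meaning, and it yields a different set from the one the hypothesis needs.

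A reader might infer that the study would report no association if its hypothesis were true. The documents do not support that. Milk adipokines are a main exposure, and the sample size is framed on them. The mixed-model plan covers adipokine concentrations together with development scores and depressive symptoms, so an analysis of milk against neurodevelopment does not depend on the plasma coefficient. Nor does the Introduction say that plasma acts only through milk. It says the concentrations are correlated, and it also asks about the role of adipokines in the context of maternal mental health, which could be another route. The near-zero results above follow from setting *c* = 0 and measuring milk without error.

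A reader might also infer that milk, leptin and the maternal outcome are left out of the analysis, or that this one set will be applied to them. Neither is stated. They are absent from the named target, not from the study, and a condensed article may leave their adjustment sets to the full protocol.

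**Conclusion.** The point holds, limited to the plasma adiponectin–neurodevelopment model. As worded, the adjustment rule targets a direct effect, while the study's hypothesis makes milk adiponectin a mediator. Following the rule removes *a* × *b* from the plasma estimate: 1.5 to 2.1 points per SD under the assumed 3 points per SD of milk and correlations of 0.5 to 0.7. Complete loss of the plasma effect needs the further assumption that plasma acts solely through milk.

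The conclusion rests on two readings: that direct effect carries its usual meaning in a causal diagram, and that the hypothesised plasma–milk–infant chain will be drawn in that diagram. The size depends on the assumed effect and correlations, because the documents give neither.

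A related caution follows. A set derived for plasma adiponectin and neurodevelopment is specific to that pair. Milk mediates the plasma–infant relation, whereas plasma may confound the milk–infant relation, so the same set cannot be presumed right for the milk, leptin or depressive-symptom models.

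**What to change.** In Data entry and statistical analysis, replace direct effect with total effect as the target for plasma adiponectin and infant neurodevelopment. State that, when plasma is the exposure, milk adipokine concentrations and any other variable the diagram places as a mediator stay out of the adjustment set. The diagram should declare the role given to maternal depressive symptoms, since the Introduction links them to plasma adipokines.

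If a direct effect is also of interest, report it as a labelled secondary mediation analysis alongside the total effect.

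Derive separate adjustment sets for the milk adipokine models, the leptin models and the maternal depressive-symptom models, and do not reuse the plasma adiponectin set for them. Settle all of this before the outcome data are analysed, so that the choice between total and direct effect cannot be guided by results.

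The cost is a change of wording and a few more diagrams. It needs no new data, visits or participants.
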